### Secondary outcomes

The study will sample three domains of possible outcomes: interpretation bias, clinical symptoms and stress/distress. For each we will collect information on (1) comprehensibility and suitability and (2) variance estimates by calculating standardised treatment effect sizes (Cohen’s *d*) and their confidence intervals.

Interpretation bias will be measured using the:
*Similarity Rating Task (SRT)* [41]. This is a standard test used to measure interpretation bias. Items describe ambiguous social scenarios that permit either paranoid- or non-paranoid interpretations and were developed by Savulich et al. [17], based on Freeman and Garety’s [46] definition of paranoia as a person’s belief that intentional ‘harm is occurring, or is going to occur’. Items are shown to have sensitivity to detect differences between high-paranoid and low-paranoid groups of participants who were found to differ in their interpretation bias on paranoid item content [17], such that the high-paranoid group showed a significantly more maladaptive pattern of interpretation (reduced endorsement of positive and non-paranoid interpretations) compared with the low-paranoid group

For the ‘encoding’ part of the task participants read 12 ambiguous passages, complete one of the last word’s missing letters and answer a comprehension question. An example of such a passage is entitled ‘car park’, followed by ‘You have parked your car in the supermarket car park and just done your weekly food shopping. On your return to your car you notice a man sat in a nearby car. He is sitting alone and looking out the w-nd-w.’ Hence, for each item, the third sentence ends with a word that has several letters missing. Participants are asked to indicate the first missing letter. For the ‘Car park’ example, the letter ‘i’ would have to be indicated to show that the last word was ‘window’. In order to check that participants correctly encoded the passage, they had to choose ‘yes’ or ‘no’ as an answer to a comprehension question, such as ‘Have you just been to the supermarket?’ which would be correctly answered with ‘yes’ in the ‘Car park’ example. Participants are given feedback on the screen about the correctness of their response to this comprehension question.

For the ‘recognition’ part of the task, participants are given four sentences, two of which represented ‘targets’ that capture a paranoid (T−) and a non-paranoid (T+) interpretation of the original passage, respectively. The other two sentences represent ‘foils’ that contain either paranoid- or non-paranoid content that is unrelated to the corresponding passage. These foils are used to control for response bias which refers to the tendency to, for instance, endorse information that is congruent with a paranoid schema rather than actually interpreting the specific item in a paranoid way [17]. For the ‘Car park’ example, the corresponding target paranoid interpretation is ‘The passenger does not want to sit next to you’ (T−) and the corresponding non-paranoid interpretation is ‘The passenger wants more legroom’ (T+). ‘Your friend is ignoring you’ and ‘Your friend is busy at work’ represent a paranoid foil (F−) and a non-paranoid foil (F+), respectively. Participants are asked to rate ‘how similar in meaning from 1 = very different in meaning to 4 = very similar’, each of the four sentences is to the corresponding original passage. By comparing participants’ ratings of each of the four sentences, we can infer their spontaneous interpretation of the original passage. Interpretation bias scores can be calculated as described above (T+ minus T−) for the screening version of this task.
*Scrambled sentences task (SST)* [47, 48]*.* In this pen-and-paper task participants are presented with ‘nonsense’ sentences, each comprising six words and are asked to select and re-order five of these words to create a grammatically correct sentence. For example, ‘pleasant to people hostile me are’ could become ‘people are hostile to me’ (paranoid interpretation) or ‘people are pleasant to me’ (non-paranoid interpretation). There are fifteen sentences in total and participants have 5 min to complete as many as possible. The order of words selected is indicated by participants writing the numbers ‘1’ to ‘5’ above the words. Instructions to participants ask them to ‘choose whatever comes to mind first’ and form statements rather than questions. Before unscrambling the 15 sentences, participants are asked to memorise a six-digit number (e.g. 615239) which they are told to keep in mind while doing the task and which they are asked to recall after completion of the task. Rude et al. [47] showed that the addition of this cognitive load makes the task more sensitive to detecting interpretation biases possibly because it stops participants suppressing biases. For instance, negative interpretation bias on the *SST* only predicted depression if the *SST* was performed under cognitive load [47]

Two values are recorded: (a) the total number of grammatically correct sentences created with a paranoid meaning is recorded for each participant (including those using fewer than five words, such as ‘people are hostile’) and (b) the total number of items attempted within the available time. From these values a negative (paranoid) interpretation bias score is calculated as a proportion: [A/B] × 100. Bias scores, therefore, range from 0 to 100, with higher values reflecting bias favouring paranoid interpretations.
*Cognitive Flexibility Scale (CFS)* [49]. This self-report measure consists of 12 items that participants rate on a 6-point scale ranging from 1 (strongly disagree) to 6 (strongly agree). It measures the three components of cognitive flexibility: (a) awareness that in any given situation there are options and alternatives available, (b) willingness to be flexible and adapt to the situation and (c) self-efficacy in being flexible

Psychotic symptoms are measured at baseline using the *PANSS* [40] conducted by a trained clinical psychologist. This is a 30-item clinical tool that measures symptom severity in psychosis. It consists of three subscales with seven items for positive symptoms, seven items for negative symptoms and 16 items for general symptoms. Each symptom is rated on a 7- point Likert scale from 1 (symptom absent) to 7 (symptom extreme), with a minimum score of 7 and a maximum score of 40 for the *PANSS* subscales; and a minimum score of 16 and a maximum score of 112 for the general symptoms.

Specifically, severity of paranoid symptoms is assessed by *PANSS* item 6 (P6 Suspiciousness/Persecution) which can be used in isolation to evaluate degree of clinical paranoia. This item measures unrealistic or exaggerated ideas of persecution using a 7-point Likert scale where 1 = absent; 2 = minimal, may be at upper extreme of normal limits; 3 = mildly symptomatic, then incrementally upwards to 7 = extreme persecutory delusions.

In addition to the *PANSS* item 6, the following self-report scales will be used to assess paranoid symptoms: the *Paranoia Scale* [50], the *Paranoid Thoughts Scale* [51] and the *Peters Delusions Inventory* (*PDI-21*) [52]. Although the latter is not a clinical symptom measure, it includes subscales reflecting clinically important elements of delusional ideation: degree of delusional conviction, frequency of delusional thoughts and degree of associated distress.

Symptoms of depression/anxiety are assessed using the *Hospital Anxiety and Depression Scale (HADS)* [53].

Stress/distress is assessed using three measures:
*Virtual Reality Environment* (*VRE*). Participants wear a headset through which they view a three-dimensional social scene populated by neutral characters (a cafe). Participants spend approximately 4 min in the virtual environment and can move through the virtual environment by walking and whole body turning. *Visual Analogue Scale* (*VAS*) measures of state mood assess how anxious, sad, paranoid and friendly participants feel and are given immediately before and after experiencing the virtual environment. Participants also complete the *State Social Paranoia Scale* (*SSPS*) [54]. The 10 items for this measure of recent paranoid thinking contain both elements of threat and intention (e.g. ‘Someone had it in for me’, ‘Someone stared at me in order to upset me’, ‘Someone was trying to isolate me’, ‘Someone was trying to make me distressed’). Each item is scored on a 5-point scale (Do not agree – Totally agree). Higher scores indicate greater levels of persecutory thinking [13, 55]
*Laughter task* [56]. Two experimental events are presented during the testing session. These are (a) an interruption by a female stooge calling the experimenter out of the room and (b) following the exit of the stooge and the experimenter, a 35-s audio recording of male and female laughter played outside the room. The recording is played using an iPad and is identical for each participant. The laughter was piloted in a sample of five individuals (without a history of mental illness and with English as a first language) to ensure that it was audible to those inside the room without sounding so loud so as to seem artificial. The aim of the task is to expose participants to two ‘real-life’ events that are inherently ambiguous by nature. At the end of the testing session participants are asked a series of questions to assess their explanations for these two events. Verbatim explanations given by individuals for each of the events are rated for the presence of a paranoid attribution (an idea of reference or an idea of persecution)
*Visual Analogue Scales*. Anxious, sad, paranoid and friendly state mood will be assessed using a simple *VAS* pre and post each training session to determine the immediate subjective impact on participants of taking part in the intervention. Furthermore, the academic literature suggests that state emotion may influence paranoia-relevant biases [57] and intervention effects might, therefore, be moderated by emotional experience during training

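### The Scrambled Sentences Task score divides grammatical paranoid sentences by all items attempted, so each ungrammatical attempt is scored as if it were non-paranoid

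*Protocol article*

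**What the plan says.** The SST is described in the Protocol article under Secondary outcomes as one of three interpretation-bias measures, with the Similarity Rating Task (SRT) and the Cognitive Flexibility Scale. On its length and time limit the text says: "There are fifteen sentences in total and participants have 5 min to complete as many as possible". Participants do it while holding a six-digit number in memory.

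Two values are recorded. The numerator A is "the total number of grammatically correct sentences created with a paranoid meaning", and short sentences qualify too ("including those using fewer than five words"). The denominator B is "b) the total number of items attempted within the available time". The scoring rule is "a negative (paranoid) interpretation bias score is calculated as a proportion: [A/B] × 100". The reading given to the result is: "Bias scores, therefore, range from 0 to 100, with higher values reflecting bias favouring paranoid interpretations".

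No count of valid non-paranoid sentences is recorded, and no rule takes ungrammatical attempts out of B. The Procedures section places the SST at baseline (T0) and at the end of treatment (T1).

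**The concern.** The numerator and the denominator refer to different sets of responses. A response enters A only if it is grammatical and paranoid; any attempt enters B. A failed attempt says nothing about how the participant interprets ambiguity, but it pulls the score towards the non-paranoid end. Two participants with different interpretation patterns can then receive the same score, and two with the same pattern can receive different scores.

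This matters because of how the pilot's figures will be used. Secondary outcomes asks for Cohen's d with confidence intervals in each outcome domain. The section on the feasibility, double-blind randomised controlled trial lists interpretation bias among the candidate primary outcomes for the next trial, to be chosen partly on observed effect sizes. Statistical analysis carries the observed variance into that trial's sample size. An SST score that mixes interpretation with sentence-building errors is a poorer basis for those decisions than one restricted to valid sentences.

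**Working it through.** **Inputs from the Protocol article (Secondary outcomes).** At most 15 items; score = 100 × A/B; A and B as defined there; stated range 0 to 100.

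**Input not in the document.** The number of ungrammatical attempts, u. I assume 0 to 5 out of 15 and show the range.

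**Step 1: the stated range.** 100 × 0/15 = 0 and 100 × 15/15 = 100, so the range reproduces. The upper end is reachable only when every attempt is grammatical.

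**Step 2: the score with errors.** Let θ be the paranoid share of grammatical sentences. Then A = θ(B−u), and

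stated score = 100 × θ × (B−u)/B.

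With grammatical sentences as the denominator, the score is 100 × A/(B−u) = 100 × θ, whatever the value of u.

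**Step 3: numbers for B = 15.**

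| u | (B−u)/B | θ = 0.4 | θ = 0.6 | θ = 1.0 (maximum) | Difference, θ = 0.6 minus 0.4 |
|---|---|---|---|---|---|
| 0 | 1.000 | 40.0 | 60.0 | 100.0 | 20.0 |
| 2 | 0.867 | 34.7 | 52.0 | 86.7 | 17.3 |
| 3 | 0.800 | 32.0 | 48.0 | 80.0 | 16.0 |
| 5 | 0.667 | 26.7 | 40.0 | 66.7 | 13.3 |

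The relative reduction is u/B, from 0 to 5/15 = 33%. With the alternative denominator, every row reads 40, 60, 100 and 20.

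**Step 4: two participants with the same score.** Six paranoid, 4 non-paranoid and 5 ungrammatical sentences give 100 × 6/15 = 40. Six paranoid, 9 non-paranoid and none ungrammatical also give 100 × 6/15 = 40. The paranoid shares of valid sentences are 6/10 = 60% and 6/15 = 40%.

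**Step 5: unequal error rates.** Suppose both arms have θ = 0.6, with u = 2 in one and u = 5 in the other. The scores are 52.0 and 40.0, an apparent difference of 12.0 points where the true difference is zero. This shows the mechanism only; the document gives no reason to expect that gap.

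**Step 6: slowness.** Items not reached are outside B. With u = 0 and θ = 0.6 the score is 60.0 at 15, 10 or 5 attempts.

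**The case against.** The scoring rule itself is not in dispute. The strongest case on the other side concerns its size and consequences.

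- **Error rate.** A reader might infer that failed attempts are frequent, given the time limit, the memory load and the patient group. The document does not show this. It excludes severe cognitive impairment and illiteracy, requires stable medication, and credits short grammatical sentences. At u = 1 of 15 the relative reduction is only 1/15 = 7%, and at u = 0 there is none. This stands: the size is unknown.
- **Poor performance in general.** A reader might infer that any weak performance would pass for low paranoia. It would not, because the attempted-items denominator already allows for speed. Only ungrammatical attempts matter.
- **Practice.** A reader might infer that fewer errors at T1 would make patients appear to worsen. That is a change within one arm. The trial compares randomised arms, the control procedure is described as matching CBM-pa apart from the active content, and sentence sets are counterbalanced. Practice should be largely common to both arms, so the main expected effect on the contrast is attenuation.
- **Variance.** A reader might infer that the rule necessarily inflates the variance estimate. If (B−u)/B were the same for everyone, difference and standard deviation would shrink together: the raw variance would fall and Cohen's d would not change. Only variation in u between people puts task error into the variance, and its amount cannot be derived from the document.
- **Reach.** Eligibility, minimisation, the interim bias assessments and the named efficacy model use the SRT, not the SST. This stands and limits the consequence.
- **Detail held elsewhere.** A scoring manual or analysis plan might define attempted more narrowly. That would not remove the point, because the article states a complete formula. If attempted was meant as validly completed, the wording needs correcting.

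**Conclusion.** The point holds as a scoring defect of limited reach. As written, each ungrammatical attempt counts as a non-paranoid sentence, and the score equals the paranoid share of valid sentences multiplied by (B−u)/B. That much follows from the formula without any assumption.

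The size rests on the assumed u. Over the range shown, the loss runs from nothing to one third of the score. Equal error rates in the two arms would shrink a raw-score difference without creating a false one; unequal rates would bias the contrast, tilting the arm with more errors towards looking less paranoid. The document supports no claim about which of these will occur.

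The change is worth making because it is cheap and brings the score into line with the construct it is meant to measure.

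**What to change.** Define the SST score as 100 × paranoid grammatical sentences / all grammatical sentences (paranoid plus non-paranoid), keeping the present allowance for short sentences and applying it to both kinds. Count ungrammatical attempts separately and report them by arm and visit (T0 and T1). Keep the attempted-items score as a sensitivity result.

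The two values now recorded are not enough to compute this, since the valid non-paranoid count is missing. It can be recovered from the paper sheets, on which participants number the words they choose, so no new data collection is needed. The cost is some rescoring time and noisier scores for participants with few valid sentences; the number of valid sentences should therefore be reported alongside the score.

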#### Procedures

The assessment procedure is outlined in Fig. 2. The first contact with participants is during screening, where we check for participants’ eligibility by assessing the inclusion and exclusion criteria described above. Based on this screening contact, researchers complete a capacity assessment to confirm that they perceived participants to understand and retain information sufficiently to make an informed choice about taking part in the study. Following informed consent, baseline assessment (T_0_) will be completed prior to randomisation, at the start of session 1, and will include measures of:Sociodemographic information such as age, gender, ethnicity, IQ [58], educational level, employment and relational statusParanoid beliefs (*SRT*, *SST* and *CFS*). Twelve *SRT* items and their corresponding comprehension questions are presented at a pace that is determined by the participant. The order of items is randomised. Participants then answer similarity ratings questions entitled by the corresponding 12 *SRT* items. Moreover, two sets of 15 scrambled sentences, taken from Savulich et al. [17], are counterbalanced across participants, so that half of participants received *SST* set 1 while the other half received *SST* set 2. Whether or not participants perform the *SRT* before the *SST,* or vice versa, is counterbalanced: half of participants perform the *SRT* first, while the other half performs the *SST* first, in order to minimise potential effects that one task might have on the performance on the other taskClinical symptoms assessed using the *PANSS*, *Paranoia Scale*, *Paranoid Thoughts Scale*, *PDI-21* and *HADS*, as well as the *Structured Clinical Interview for DSM-5* (*SCID-5*) [59] will be conducted by a trained Clinical Psychologist (AT) during baseline assessment

After receiving the intervention (CBM-pa or text-reading control) interim assessment (T_i1–5_) includes at each time point:Paranoid beliefs measured using a total of eight items of the *SRT*
Paranoid symptoms assessed by *PANSS* item 6 (P6 Suspiciousness/Persecution) only

At week 6, after receiving the intervention, the assessment (T_1_) includes measures of:Paranoid beliefs (*SRT*, *SST* and *CFS*). As for T_0_, *SRT* and *SST* contain the same number of items (12 and 15, respectively) and are counterbalanced across participantsClinical symptoms (*PANSS* item 6, *Paranoia Scale*, *Paranoid Thoughts Scale*, *PDI-21* and *HADS*)Vulnerability to stress using the *Laughter Task* and *VRE* in counterbalanced order

Participants will be contacted at 1 and 3 months from end of the session 6 for follow-up assessments (T_2_–T_3_) which include:Paranoid beliefs measured, using a total of 12 items from the *SRT*
Clinical symptoms (*PANSS* item 6, *Paranoia Scale*, *Paranoid Thoughts Scale*, *PDI-21* and *HADS*).

## Data monitoring

The researchers involved in the study will enter data into an SPSS spreadsheet. There will be four separate spreadsheets for each assessment phase (baseline, interim, end of intervention and follow-ups). The data will be stored on a locked group drive, only accessible to researchers in the ‘Emotion and Cognition’ group at IoPPN, King’s College London.

The separate SPSS spreadsheets will be merged, once all data have been entered and checked. The randomisation data and trial data will only be linked once all data collection is complete. All databases will be organised according to anonymised participant ID number (assigned at baseline) which will ensure that the databases are merged correctly.

## Risk management

Capacity to consent is assessed via a standard written protocol approved by the Ethics Committee [43]. The clinical psychologist will assess and ensure the safety of participants throughout the course of the study. A Risk Assessment Form has been developed and adapted from the protocol used at the Psychological Interventions Clinic for outpatients with Psychosis (PICuP) in order to minimise any potential adverse events. The study has been assessed as low risk, however, the *VRE* and *Laughter Task* could be perceived as mildly stressful for those experiencing paranoia. To address this, the nature of the task, including the option to withdraw, will be described in writing (Information Sheet) and reiterated verbally immediately prior to the relevant session. Mood state will be assessed before leaving and at follow-up contact. Any adverse events and serious adverse events will be recorded and reported in full in the trial report/journal paper. Any adverse events, defined as any events that result in death, serious injury or hospitalisation, which are considered by the chief investigator or Trial Management Group (TMG) to be related to trial procedures in any way, or are unexpected in that they are not listed in the trial protocol, will be reported promptly to the sponsor and the Ethics Committee.

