**Fig. 1 Fig1:**
[figure not shown]
Trial flow diagram

Groups should be equalised on the expectation of benefit because the introduction to each trial arm is delivered by computer and standardised across the two conditions. Expectation of benefit will be assessed using the *Credibility and Expectancy Questionnaire* [45]. The intervention will be delivered on laboratory-owned laptops.

Qualitative interviews (*n* = 8) will be conducted after the end of quantitative data collection, providing an in-depth assessment of participants experience of the intervention, including potential side effects (e.g. unexpected emergence, rather than amelioration of paranoid thoughts).

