### Primary outcomes

As the study is a feasibility evaluation of the CBM-pa intervention there is no single primary outcome measure. Instead, feasibility will be assessed on the basis of rates of recruitment, consent, dropout and follow-up. In addition, acceptability of randomisation will be examined, including the integrity of double-blinding. Qualitative interviews will be conducted after the end of quantitative data collection, using a purposively selected subsample of eight active-arm patients. Purposive selection will represent sample variation in the following priority order: gender, severity of paranoia, severity of bias, age and ethnicity. The aim is to explore acceptability, barriers to participation, promoting engagement and optimum form of delivery of the intervention.

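### The only definition of an adverse event is a list of seriousness criteria, which conflicts with the sentence before it and leaves non-serious emergence of paranoia outside adverse event reporting

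*Protocol article*

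**What the plan says.** Two consecutive sentences in Risk management (protocol article) matter here. The first makes a general commitment: "Any adverse events and serious adverse events will be recorded and reported in full in the trial report/journal paper". The second opens with "Any adverse events, defined as any events that result in death, serious injury or hospitalisation". It goes on to say that such events, if judged related to trial procedures or unexpected, "will be reported promptly to the sponsor and the Ethics Committee". The article gives no other definition of either term.

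The Interventions section, in the text after Fig. 1, describes eight qualitative interviews that will cover potential side effects, and its example is "unexpected emergence, rather than amelioration of paranoid thoughts". These interviews "will be conducted after the end of quantitative data collection". Primary outcomes adds that they are done "using a purposively selected subsample of eight active-arm patients".

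Paranoia is also measured quantitatively, with no restriction to one arm in the text:

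- Procedures lists, at each interim assessment after either intervention, "Paranoid symptoms assessed by *PANSS* item 6 (P6 Suspiciousness/Persecution) only".
- Secondary outcomes describes visual analogue scales (VAS) for anxious, sad, paranoid and friendly mood before and after every training session.
- Procedures repeats PANSS item 6, three self-report paranoia or delusion scales and the HADS after treatment (T1) and at the 1- and 3-month follow-ups (T2, T3).
- Risk management adds a mood check before participants leave and at follow-up contact.

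**The concern.** The first sentence treats adverse events and serious adverse events as different things. The second defines the broader term by criteria that belong to the narrower one. A team following the stated definition would not log a patient whose suspiciousness or distress rose during training unless death, serious injury or hospitalisation followed.

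That matters for this intervention. Patients with persistent, distressing paranoia read scenarios whose severity is designed to rise from session to session (CBM-pa procedure and item development), and the article itself anticipates that paranoid thoughts might emerge. An adverse event section reporting no events would then be compatible with a minority having worsened. A feasibility trial is where the harm definition and its recording should be tested before a full trial inherits them.

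**Working it through.** **The text.** There is no planned figure to reproduce, so the first check is of wording.

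1. Sentence one: adverse events and serious adverse events are both recorded and both published, so there are two categories.
2. Sentence two: the term adverse events is defined by death, serious injury or hospitalisation. Under that definition every adverse event is serious, and the first category is empty apart from the second.
3. Emergence of paranoid thoughts without one of those three consequences falls outside the definition, although the Interventions section calls it a potential side effect.

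**Stated use of the paranoia and mood data.**

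| Data | Collected in | Stated use |
|---|---|---|
| PANSS item 6 at each session | both arms | dose-response, number of sessions (Outcome measures and timeline) |
| VAS before and after each session | no arm restriction | immediate subjective impact, possible moderation (Secondary outcomes) |
| Symptom scales at T1, T2, T3 | both arms | effect sizes and variance estimates (Secondary outcomes) |
| Mood check before leaving and at follow-up | no arm restriction | individual risk management |
| Interviews, n = 8 | active arm only | experience, including side effects |

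Only the last row names emergence of paranoia as a side effect. The only threshold for change in Statistical analysis is a drop of at least 20%, used for the future sample size. No count of patients who got worse is stated.

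**Scale.** The documents give no rate of emergent paranoia, so the true rate p is an assumption, shown over a range. The interview sample is purposive, and treating it as random is a second assumption. With 60 patients randomised 50:50, there are about 30 per arm.

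Chance of at least one case among n patients = 1 − (1 − p)^n:

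| p (assumed) | n = 8 | n = 30 |
|---|---|---|
| 5% | 1 − 0.95^8 = 34% | 1 − 0.95^30 = 79% |
| 10% | 1 − 0.90^8 = 57% | 1 − 0.90^30 = 96% |
| 20% | 1 − 0.80^8 = 83% | 1 − 0.80^30 = 99.9% |

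If no case is seen, the one-sided 95% upper limit is 1 − 0.05^(1/n): 31% for n = 8 and 9.5% for n = 30. These figures compare eight interviews with the whole active arm as places to look for the side effect. They are not the trial's overall chance of detecting worsening, because the quantitative measures also exist.

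**The case against.** The strongest reply is that the two sentences describe two tiers: all events are recorded and published, and the serious ones that are related or unexpected are also sent promptly to the sponsor and the Ethics Committee. The main verb of the second sentence supports that reading, and it may well be the intent. But the text uses the same term in both tiers and defines it once, with seriousness criteria, so a reader cannot tell which tier the definition governs. If two tiers were meant, the correction is a change of term.

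A reader might infer more: that emergent paranoia is looked for only in the eight interviews, or that the trial can make no comparison with control. The documents do not support either. PANSS item 6 at each session, the paranoia VAS around each session and the T1 to T3 scales would show worsening in both arms, and effect sizes with confidence intervals are planned for the symptom and distress domains. The VAS purpose, immediate subjective impact, is close to a safety purpose. What remains is that these data are not counted or reported as harm, and an average effect can conceal a minority who worsen.

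Oversight also exists. A clinical psychologist attends to safety throughout, a Risk Assessment Form has been developed, and the Trial Steering Group reviews participant safety, feedback and complaints. These protect individuals during the trial, but they do not settle what is counted as an adverse event in the report.

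Finally, a journal article may leave safety tables and detailed definitions to a fuller document. That is fair for the table, which is offered here as an improvement. It does not excuse the definition, which the article does state and which conflicts with its neighbouring sentence.

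**Conclusion.** The point holds in a limited form. The stated definition is inconsistent with the preceding commitment and, taken literally, excludes non-serious emergence or worsening of paranoia from adverse event reporting. The data to compare worsening between arms are collected; the article states no plan to use them that way. As a named side effect, emergence is explored only in eight active-arm patients, with no control counterpart.

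The size depends on an unknown rate. Over assumed rates of 5% to 20%, moving from eight interviewees to the full active arm raises the chance of seeing at least one case by 45, 39 and 17 percentage points (79 − 34, 96 − 57, 99.9 − 83, rounded). This takes the purposive sample as random and all 30 active-arm patients as assessed. No efficacy or feasibility estimate is affected.

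**What to change.** 1. Reconcile the two sentences in Risk management. Attach death, serious injury and hospitalisation, together with the existing prompt-reporting rule, to serious adverse events. Define adverse events as any untoward occurrence, including non-serious worsening of paranoia or distress. The prompt-reporting rule itself stays as it is.
2. Report by arm, from data already collected, the number and percentage whose PANSS item 6 worsened from baseline at each assessment, with confidence intervals and the number assessed as denominator. State in advance the amount that counts as worsening: on a single 7-point item, counting any rise would include rating noise.
3. In the same table, give the pre-to-post session change in the paranoid, anxious and sad VAS by arm, with confidence intervals.

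The cost is a wording change, slightly more event recording and one descriptive table. With about 30 per arm the table will be imprecise (even zero cases among 30 leaves an upper limit of 9.5%), so it should be presented as description and not as a test. The interviews can stay as planned.
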